**Methods/Design:**

Cluster randomised controlled trial with 20 general practitioners and 20 physiotherapists in primary care as the unit of randomisation. Each practitioner will recruit up to 10 patients, aged 20 to 55 years, with non-specific sub-acute/chronic LBP of more than four weeks but less than 1 year's duration. Practitioners in the intervention arm will provide cognitive patient education intervention in up to four weekly sessions, each lasting 30 minutes. Practitioners in the control arm will provide normal treatment, but have to make four appointments for the patients. Patients, outcome assessors, and study statistician will be blinded to group allocation.

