### Recruitment of practitioners

An invitation to an information meeting regarding the project was sent out to all GPs and PTs working in the primary health care in Oslo and Akershus County in Norway in March 2008. After an information meeting, the practitioners were invited to participate in the study. A total of 20 GPs and 20 PTs were included and randomised.

Strategies to promote participation of practitioners into the trial included offering professional development points and financial compensation for the extra time spent on recruiting patients to the project, as well as treatment of included patients.

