### Recruitment of patients and eligibility criteria

Each participating GP and PT in both intervention and control groups will consecutively ask eligible patients to participate in the study. The study is thus taking place in a normal clinical setting. The inclusion criteria are:

• Men and women aged 20 - 55

• Unspecific LBP

• Duration from 4 weeks up to 1 year since onset of actual pain episode

• Signed informed consent

• A score ≥ 4 on the Roland Morris Disability Questionnaire

The following criteria excluded patients from participation:

• Provider's uncertainty of diagnosis; possible nerve root pain or severe pathology

• Signs of any 'red flags'

• Particular interest in or demand for a specific treatment

Consequently, all patients visiting his or her provider because of back pain will be assessed according to these inclusion and exclusion criteria. If the patient is found eligible, he or she will be asked to participate. Those who agree to participate will sign a consent form and receive the questionnaires described later. The patients may either answer the questionnaires immediately in the provider's waiting room, or at home. In both cases the forms will be sent in a stamped and addressed envelope before the first session of the trial. The provider will inform the study management by an enrolment fax and arrange for the first session within a week of inclusion. Those who do not want to participate in the study or fail to satisfy the criteria will be registered by initials, year of birth, score on the Roland Morris Disability Questionnaire and the reason for not participating. All the procedures are identical for both intervention and control groups.

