### Intervention group

The professionals have been trained in the specific model of LBP treatment based on the biopsychosocial understanding of LBP and the "intensive neurophysiology education". Following this training they will provide their LBP patients in their normal clinical settings with a four-session treatment programme consisting of this education programme in addition to their normal treatment. At each treatment session the caregiver will stick to the procedures described in detail in the trial manual when communicating with the patient.

The "intensive neurophysiology education" programme has been developed by a group of British and Australian researchers as an education programme for patients with LBP. The cognitive elements of this programme consist basically of an understanding of pain that differs somewhat from the traditional "injury model". This theory is primarily based on the neurophysiology of pain, reflected by sensitisation and neuronal response to inactivity and movement control [27]. Based on this, the education programme has three basic elements [28]:

• Reduction of what the patients perceive as threatening inputs to the brain

• Targeting the patients' own understanding of the pain

• Exposure to the threatening inputs

Previous studies have documented an additional effect of "intensive neurophysiology education" when combined with physiotherapy [27].

The intervention will be given as four 30-minute sessions once a week for four consecutive weeks. This treatment is specified in a manual for this trial and all intervention doctors and physiotherapists have attended the 18 lessons course. They are also provided with a written summary of the content of each session.

Each of the sessions has a specific content of education and discussion in the one-to-one setting between the provider and the patient. Initially the discussion concerns the thoughts and fears of the patients and their LBP. Eventually, the education programme will deal more and more with exposure to movements and daily activities that the patients more or less deliberately avoid because of fear of provoking pain. As homework between the sessions, the patients will be asked to identify barriers to normal functioning, reasons for fear avoidance behaviour and other reflections related to the education. They will also be asked to make specific registrations regarding function, pain and work absence.

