### Control group

The providers of the control group are asked to register and include all patients meeting the inclusion criteria in a similar manner. These patients will also answer on all questionnaires, and will meet their provider weekly for up to four weeks. These sessions have no defined content, but the providers will spend somewhat more time on these patients than the regular schedule, asking for more details on what prevents them from resuming normal activity. The control group providers have not participated in the training course of the intervention and therefore their care will consist of whatever is the normal procedure for the individual doctor or physiotherapist, only that the time spent for each patient will be somewhat longer than normal (particularly for the doctors). This is done to minimise the effect of the increased attention in itself so that any observed differences between the groups are more likely to be due to the "intensive neurophysiology education".

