### Data analysis

A daily checking for accuracy and completion of data forms and double data entry will be used to ensure quality of the data. Data will be analysed by a statistician who is blinded to group status. The primary analyses will be by intention-to-treat and we will restrict the number of analyses in order to reduce the possibility of Type I errors. For primary outcomes, a p value of < 0.05 will be considered statistically significant. For the secondary outcomes a p value of < 0.01 will be considered statistically significant.

Differences between the groups will be presented as a mean with 95% CI or in categories with odds ratio for categorical data. For the primary outcome of days to return to work a survival curves analysis with a log-rank statistic will be used to assess differences between the groups, and Cox's regression to assess the effects of treatment (group) status on hazard rates for time to return to work. A mixed model with group as a fixed factor will be used for the other outcome measures. If there is a significant difference between treatment groups, post-hoc analyses will be conducted. We will also test for potential confounding factors in these models. Analyses of prognostic factors will be carried out by multivariate regression models.

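### Unblinded providers recruit patients after randomisation, and the plan makes adjustment of the RMQ comparison conditional on testing for confounders; baseline RMQ and provider type should always be in the primary model

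*Protocol article*

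**What the plan says.** All places are in the protocol article.

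- **Order of events.** Recruitment of practitioners reports randomisation as complete: "A total of 20 GPs and 20 PTs were included and randomised". Patient recruitment is described as still to come: "Each participating GP and PT in both intervention and control groups will consecutively ask eligible patients to participate in the study".
- **Knowledge of arm.** Under Intervention group, "all intervention doctors and physiotherapists have attended the 18 lessons course"; under Control group, "The control group providers have not participated in the training course of the intervention". The abstract's statement on blinding is "Patients, outcome assessors, and study statistician will be blinded to group allocation". Providers are not on that list.
- **Discretion.** The eligibility section excludes patients when the provider doubts the diagnosis, and also for "Particular interest in or demand for a specific treatment". The provider applies both.
- **Safeguards in the same section.** Patients are approached consecutively, everyone attending with back pain is assessed, RMQ must be at least 4, and procedures are the same in both arms. Patients who decline or are ineligible are logged with, among other items, their "score on the Roland Morris Disability Questionnaire and the reason for not participating".
- **Analysis.** Data analysis specifies a mixed model with group as the only named fixed factor for outcomes other than return to work, and then adds "We will also test for potential confounding factors in these models". Data collection shows that baseline values of the outcomes, the Örebro questionnaire and work status are recorded.

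**The concern.** Randomising 40 providers balances providers. It balances patients only if recruitment is unaffected by the arm. Here the person who decides whether a patient qualifies, and who asks for consent, knows the arm. The exclusion for treatment preference is one that a provider newly trained in an education programme could apply differently from an untrained colleague. Any resulting patient imbalance would be systematic and would not shrink as more patients are recruited.

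Baseline adjustment can remove the measured part of such an imbalance, provided it is always made. The quoted sentence makes it depend on a test of unnamed factors. A reader therefore cannot tell whether the primary RMQ estimate will be unadjusted, adjusted for baseline RMQ, or adjusted for whatever the tests suggest. That fits poorly with the same section's aim of keeping the number of analyses small.

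**Working it through.** The plan gives no figure for recruitment bias, so there is none to reproduce. The calculation below shows scale only.

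**Inputs from the documents.** Target difference about 2 RMQ points and SD 3 (Sample size); 20 providers per arm; 300 / 40 = 7.5 patients per provider.

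**Assumptions, not in the documents.** A selection-induced difference in mean baseline RMQ of 0.5, 1 or 2 points; a slope of follow-up on baseline RMQ of 0.3 to 0.7 (0.5 in the simulation); ICC 0.05; no true effect; no clustering of baseline RMQ.

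**Step 1: no adjustment, follow-up score.** Bias = shift × slope. For a 1-point shift:
- 1 × 0.3 = 0.3 and 1 × 0.7 = 0.7 points
- as a share of the target, 0.3 / 2 = 15% and 0.7 / 2 = 35%

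**Step 2: no adjustment, change score.** Sample size speaks of mean changes, so this version matters too. Bias = shift × (slope − 1):
- 1 × (0.3 − 1) = −0.7 and 1 × (0.7 − 1) = −0.3 points

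The size range is the same and the sign is opposite. Analysing change gives no protection, and the direction of bias depends on a choice the quoted sentence leaves open.

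**Step 3: how often a baseline test would see the shift.** The standard error of the baseline difference from provider means is 3 × √(1/7.5) × √(2/20) = 0.346. A 0.5-point shift is 0.5 / 0.346 = 1.4 standard errors, below the usual threshold of about 2, so it would often be missed. A 1-point shift is 2.9 standard errors and would usually be found.

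**Step 4: three strategies compared.** Simulation on provider means, slope 0.5, 6,000 runs per row. Cells show the size of the bias in points and the type I error.

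| Baseline shift | Never adjust | Adjust only if baseline test significant | Always adjust for baseline RMQ |
|---|---|---|---|
| 0.5 | 0.26; 10% | 0.12; 6% | about 0; 5% |
| 1 | 0.50; 25% | 0.05; 6% | about 0; 5% |
| 2 | 0.99; 71% | 0.00; 5% | about 0; 5% |

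The first column agrees with shift × 0.5 = 0.25, 0.50 and 1.00. Conditional adjustment leaves 0.12 / 2 = 6% of the target at a 0.5-point shift and 0.05 / 2 = 2.5% at 1 point.

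**Step 5: selection on something unmeasured.** If the arms differ by 0.5 or 1 point of prognosis that baseline RMQ does not capture, the bias stays at 0.5 or 1.0 under all three strategies. Type I error is then about 24–29% or 71–80%.

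**The case against.** The best defence is that the protocol already restrains selection. Consecutive invitation, assessment of everyone with back pain, a numeric RMQ threshold, identical procedures and a log of non-participants are real safeguards. This stands: a reader might infer that testing for confounders is the trial's only protection, and the documents contradict that. The safeguards limit selection or help to detect it; they do not remove discretion exercised with knowledge of the arm.

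Second, a reader might infer that bias enters through data-driven modelling. It does not. It enters through who is recruited, and the conditional model only leaves part of it uncorrected. Blinding the statistician also limits deliberate choice of a favourable model, though it does not fix which model is primary.

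Third, the sentence does not say that covariates are selected by significance, and it could describe supplementary analyses. That is fair. Selection by significance is a usual reading, not a stated rule, and the ambiguity is itself why the primary estimate is undetermined.

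Fourth, the covariate list and the tabulation of the register may sit in a fuller protocol or SAP that is not shown. Their absence from an article is not a fault. The point rests on the approach that the article does state.

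Fifth, 15 to 35% of the target might be taken as the cost of the quoted sentence. It is the cost of no adjustment at all. If baseline RMQ is among the factors tested, the illustrated residual is 2.5 to 6%. The article does not say whether it is.

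**Conclusion.** The point holds in limited form. Recruitment after randomisation by providers who know their arm is documented, so systematic patient imbalance is possible despite the safeguards. The stated analytic response makes adjustment conditional and does not settle the primary RMQ estimate.

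On the assumed inputs, the exposure is 0.3 to 0.7 points for a 1-point shift if no adjustment is made, with the sign reversed for change scores. It is roughly 0.05 to 0.12 points if baseline RMQ is tested and adjusted for only when significant. The shift, slope and ICC are assumptions. The documents do not show that selective recruitment has occurred or will occur. Because the gain over conditional adjustment is modest and costs almost nothing, this is a free improvement. It does not cure recruitment bias, because covariates cannot remove selection on unmeasured factors.

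**What to change.** Replace the quoted sentence in Data analysis with wording to this effect: *The primary RMQ model will include baseline RMQ, provider type (the randomisation stratum) and a short set of prognostic factors named in advance, such as the Örebro score and baseline work status, regardless of any significance test. Models with other potential confounders will be sensitivity analyses only.*

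Add one table from the existing register, by arm: numbers excluded and declining, the reasons, and RMQ of participants and non-participants. Say in the text that adjustment deals only with measured imbalance. The table then gives readers some evidence on selection that the model cannot correct.

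The cost is a wording change, one table and a few degrees of freedom. The named covariates and the register are already being collected, and neither the design nor patient contact changes.

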### Sample size

The primary outcome of the study is patient-reported function as measured on a continuous measure (Roland- Morris Questionnaire). Based on previous Norwegian studies using the RMQ for patients with LBP, a clinically relevant difference between two groups can be estimated to be approximately 2 points with a SD of 3. This is also similar to a previous evaluation study of the "intensive neurophysiology education" carried out by Moseley et al [27]. We put the significance level (alpha) to 5% with the probability of at least 80% to discover a difference between the two intervention groups. If the difference between mean changes in the two groups is at least 10% (approximately 2-3 points) with SD of 3, we will need approximately 50 patients in each group. Adjusting for the cluster design of 20 different clusters and loss to follow-up we end up with 150 patients in each group, total n = 300 patients, that is 75 patients in each block. It seems from this sufficient if each provider recruits 7 or 8 patients each in order to obtain 300 in total.

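### The base figure of about 50 patients per group does not follow from the stated inputs: 36-37 suffice for 80% power, and 50 gives about 91%

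*Protocol article*

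**What the plan says.** All of the calculation stands in the protocol article, Sample size.

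- Effect and SD, first statement: "a clinically relevant difference between two groups can be estimated to be approximately 2 points with a SD of 3".
- Effect and SD, second statement, in the sentence that produces the number: "If the difference between mean changes in the two groups is at least 10% (approximately 2-3 points) with SD of 3".
- Error rates: alpha of 5%, sidedness not given, and power set "with the probability of at least 80% to discover a difference between the two intervention groups".
- Base number: "we will need approximately 50 patients in each group".
- Final number: "Adjusting for the cluster design of 20 different clusters and loss to follow-up we end up with 150 patients in each group", which is 300 in total at 7 or 8 patients per provider.

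Under Recruitment of practitioners the article reports: "A total of 20 GPs and 20 PTs were included and randomised". The Outcome measures section gives the questionnaire a range of 0 to 24. The article states no ICC, design effect or loss rate.

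**The concern.** The base number is the one step of the calculation for which the article prints every input except sidedness, so a reader can check it. It does not check. The text presents 50 as what is needed for the stated power, but the printed inputs need about a quarter to two thirds fewer patients, depending on which of the stated differences is used. Either the number or the power beside it is misdescribed. The final 150 per arm is built on that number, so a reader cannot tell from the article what power or detectable difference the design was meant to have for its primary outcome.

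**Working it through.** **Inputs.** From the article: difference 2 points (also 10% of a 24-point scale = 2.4 points, or up to 3), SD 3, alpha 0.05, power 0.80, 150 per arm, 7.5 patients per provider on average. My assumptions: two-sided test; equal allocation, so 20 clusters per arm (20 × 7.5 = 150); loss between 0 and 30%; a range of ICC values.

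**Step 1: try to reproduce 50.** n per group = 2(z₀.₉₇₅ + z_power)² SD² / difference².

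- 2 points, 80% power: 2 × (1.96 + 0.8416)² × 9 / 4 = 35.3, so 36 (37 with the t-test).
- 2.4 points: 2 × 7.849 × 9 / 5.76 = 24.5, so 25 (t-test 26).
- 3 points: 2 × 7.849 × 9 / 9 = 15.7, so 16 (t-test 17).
- 2 points, 90% power: 2 × (1.96 + 1.2816)² × 9 / 4 = 47.3, so 48 (t-test 49).

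A one-sided test at 80% power needs only 28 at 2 points. No variant at 80% power gives 50.

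**Step 2: power at 50 per group.** Standard error = 3 × √(2/50) = 0.60. Then 2/0.60 − 1.96 = 1.37, and power = Φ(1.37) = 91.5% (t-test 91.0%).

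**Step 3: what the factor of 3 corresponds to.** With loss L, the analysed number per arm is 150(1 − L), the analysed cluster size is m = 7.5(1 − L), the design effect is DE = 150(1 − L)/50, and ICC = (DE − 1)/(m − 1).

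| Loss | DE | m | Implied ICC |
|---|---|---|---|
| 0% | 3.0 | 7.5 | 2.0/6.5 = 0.31 |
| 10% | 2.7 | 6.75 | 1.7/5.75 = 0.30 |
| 20% | 2.4 | 6.0 | 1.4/5.0 = 0.28 |
| 30% | 2.1 | 5.25 | 1.1/4.25 = 0.26 |

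**Step 4: power of the final design for 2 points, SD 3.** Effective n per arm = 150(1 − L)/[1 + (m − 1)ICC]; power from the noncentral t distribution with 38 df (40 clusters − 2).

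| Loss | ICC 0.05 | ICC 0.10 | ICC 0.20 | ICC 0.30 | ICC 0.40 |
|---|---|---|---|---|---|
| 0% | 99.8% | 99.2% | 96.0% | 90.6% | 84.3% |
| 10% | 99.7% | 98.9% | 95.3% | 89.9% | 83.6% |
| 20% | 99.4% | 98.4% | 94.5% | 88.9% | 82.8% |
| 30% | 99.0% | 97.6% | 93.3% | 87.7% | 81.7% |

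The lowest cell is 30% loss with ICC 0.40: 105/(1 + 4.25 × 0.40) = 38.9 effective patients per arm, power 81.7%.

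**Step 5: detectable difference at 80% power, 20% loss.** (t₀.₉₇₅ + t₀.₈₀ on 38 df) × 3 × √(2/effective n), where the t sum is 2.024 + 0.851 = 2.876. At ICC 0.05, effective n is 120/1.25 = 96, giving 1.25 points. At ICC 0.10 it is 120/1.5 = 80, giving 1.36. At ICC 0.20 it is 120/2 = 60, giving 1.58.

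**The case against.** The strongest defence is that the article asks for at least 80% power and gives only an approximate number. Fifty per group delivers about 91%, so the power floor is met. This stands, and it limits the point to a misdescribed number. It does not make 50 the number needed at that floor.

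A reader might infer more, and the documents do not support it:

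- **That the stated 80% power is missed, or that the trial is too small.** Step 4 shows the reverse on the stated difference and SD.
- **That the inflation rests on an implausible ICC.** The article gives no ICC and nothing to compare one with. The implied 0.26-0.31 depends on an unstated loss rate. A condensed article may leave both inputs to the full protocol, so their absence is not an error in itself.
- **That 150 per arm quietly covers a larger SD.** The article gives SD 3 twice and no other value.
- **That the cluster count contradicts the 40 randomised providers.** The 20 clusters appear in a sentence about patients in each group. Read per arm, they agree with 40 providers and with 7 or 8 patients each. The wording is loose, but no number is shown to be wrong.
- **That a detectable difference below 2 points is a defect.** The Data analysis section already promises mean differences with 95% confidence intervals, which a reader can set against 2 points.

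The two statements of the difference are also compatible: 2.4 points lies within 2-3, and 2 is its lower end. But they lead to base numbers from 16 to 37, so one should be named as the target.

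**Conclusion.** The point holds as a wrong base figure in the sample size calculation for the primary outcome. With a two-sided 5% test and SD 3, 80% power needs 36-37 per group at 2 points, so 50 exceeds the requirement by 13-14 patients per group. It corresponds instead to roughly 90% power. The discrepancy is on the safe side: under 20 clusters per arm and losses of 0-30%, the final design keeps more than 80% power for 2 points at every ICC up to 0.40. These design-power figures rest on the stated SD and on assumed ICC and loss values. The intended power of the design cannot be confirmed from the article. Nothing here questions the total of 300.

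**What to change.** Keep n = 300 and restate the Sample size section:

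- Name one target difference, 2 points, in place of the two statements.
- Either correct the base number to 36-37 per group for 80% power, or keep 50 and say that it corresponds to about 90% power. State that the test is two-sided, if that is what was used.
- Write 20 clusters per arm (40 in total).
- Give the power and detectable difference at 150 per arm under the ICC and loss rate actually used. If the factor of 3 from 50 is kept, that ICC should fall at about 0.26-0.31 for losses of 30% to 0%.

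The cost is a few reworded sentences. Enrolment, the number of providers and the analysis do not change.
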